### Data collection

2.10

Baseline assessment before ESD will include patient sex, date of birth, date of obtaining informed consent, and history of gastrectomy or reconstructive surgery of the gastric tract, assessment of performance status, American Society of Anesthesiologists physical status, and use of antithrombotic agents. Other assessments will include subjective findings; objective findings; and the results of hematological examinations, blood coagulation tests, upper endoscopy, and X-ray examination of the chest. Treatment parameters will be assessed on the day of ESD, and AEs will be recorded from the day of ESD to discharge 15 ± 7 days later. Physical findings and the results of blood tests and X-ray examination of the chest will be evaluated the day after ESD. Parameters assessed at discharge will include physical findings, blood examination results, and pathological results. The schedule for data collection is shown in Figure 3.

**Figure 3 F3:**
[figure not shown]
Schedule for data collection. ∗1: within 28 days before registration. ∗2: within 120 days before registration. ESD = endoscopic submucosal dissection.

## Statistical analysis

3

### Sample size calculation

3.1

Because this will be a superiority study, the sample size will be estimated based on the primary endpoint (i.e., ESD procedure time). A single center retrospective study compared a traction ESD method using dental floss and a hemoclip in 53 patients with conventional ESD in 185 patients, including propensity score matching analysis.^[25]^ That study found that the ESD procedure time was significantly shorter for the traction than for the conventional ESD group (82.2 ± 79.5 minutes vs 118.2 ± 71.6 minutes, respectively; *P* = .002).^[25]^

Calculations based on these findings showed that 142 patients were needed to ensure 80% power for a 2-sided significance level of 0.05. Assuming a dropout rate of 5%, a sample size of 150 patients has been planned.

### Statistical analysis

3.2

The primary endpoint is procedure time, defined as the time from the start of local injection into the submucosal layer to the end of detachment. The multiple regression analysis will be performed to estimate the treatment effect between groups adjusted with the stratified factors (i.e., operator proficiency, tumor size, institution and lesion location).

The secondary endpoint includes the factors associated with ESD procedure time which consist of operator proficiency (trainee vs expert), tumor size (≤20 mm vs ≥20 mm), lesion location, findings associated with UL (positive vs negative), and institution (high volume center vs low volume center); EndoTrac equipping time; time from starting traction with EndoTrac to complete resection; clip slip-off rate during EndoTrac and number of EndoTrac used; conversion rate; rate of specimen damage; histologic findings; and AE. The continuous outcomes will be summarized into the mean and standard error. When these outcomes have non-normal distribution, will be used the median and interquartile range as summary statistics. The categorical values will be summarized into frequency (proportion).

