### Randomization and blinding

2.6

Patients will be randomly assigned 1:1 to undergo conventional ESD or EndoTrac ESD. Random assignment will be centrally controlled by the Internet Data and Information Center for Medical Research cloud version (INDICE Cloud), supported by University Hospital Medial Information Network. Randomization will be performed via dynamic balancing using the minimization method, with stratification by operator experience (trainee or expert), tumor size (≤20 mm or >20 mm), tumor location (upper/middle thirds or lower third of the stomach), and institution. Neither patients nor physicians will be blinded to patient allocation.

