#### Criterion of operator

2.7.1

In this study, the operator must be a research investigator or coordinator who has performed more than 5 ESD procedures for gastric lesions, and at least 1 ESD procedure with an EndoTrac.

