EndoTrac has advantages over clip-with-line traction methods. The EndoTrac can not only control the degree of strength but the direction of traction. Use of the EndoTrac enables coordination of an appropriate direction by pulling or pushing the sheath to achieve the desired traction. The clip-with-line method can pull but not push the lesion, with this 1-way traction resulting in inappropriate or excessive traction, preventing the operator from recognizing the appropriate submucosal layer for dissection.

To the best of our knowledge, the study described herein will be the first prospective randomized control study to compare the efficacy and safety of EndoTrac ESD with that of conventional ESD for gastric tumors. Use of a randomized controlled design can reduce biases associated with retrospective studies, such as patient selection, operator selection, small sample size, and the unconscious choice to use EndoTrac.

Factors associated with technical difficulties and long procedure times for gastric ESD include larger lesion sizes, lesions located in the middle and upper two-thirds of the stomach, lesions located in the greater curvature, presence of ulceration, and an operating physician who has performed <40 of these procedures.^[2,7,8,20–22]^ To determine whether these factors are also associated with greater difficulties in patients undergoing EndoTrac ESD, we plan to randomize patients to undergo EndoTrac or conventional ESD by dynamic balancing using the minimization method, and with stratification by operator experience (trainee vs expert), tumor size (≤20 mm vs >20 mm), tumor location (upper/middle thirds vs lower third), and institution (high vs low volume center). The major limitation of this study is that the operator is not blinded to treatment group allocation.

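### The primary regression leaves out greater-curvature location, a predictor of procedure time that the protocol itself names and records, and so gives up some precision at no gain

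*Protocol article*

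**What the plan says.** Section 3.2 of the protocol article describes the primary analysis as a multiple regression of procedure time, "adjusted with the stratified factors (i.e., operator proficiency, tumor size, institution and lesion location". It does not say how each factor is coded. Section 2.6 does so for the minimization: operator experience as trainee or expert, then "tumor size (≤20 mm or >20 mm), tumor location (upper/middle thirds or lower third of the stomach), and institution".

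The Discussion lists what makes gastric ESD long and difficult. Besides larger size and middle or upper location, it names "lesions located in the greater curvature, presence of ulceration, and an operating physician who has performed <40 of these procedures". The Introduction also uses the greater curvature of the upper or middle third as its example of a difficult site.

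Section 2.9 defines tumor location both by third and by surface, with greater curvature as one of four surfaces, for a secondary analysis of procedure time. The same section takes ulcer status from pathology. Section 2.4 uses clinical ulcerative findings to decide eligibility.

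**The concern.** The Discussion names five drivers of procedure time. Size, upper/middle location and operator experience are in the minimization and the primary model. Greater curvature and ulceration are in neither.

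Greater curvature matters most here. The Introduction and Discussion report that a randomized trial of another traction method found no overall reduction in time, but did find one for greater-curvature lesions of the upper and middle thirds. The upper/middle versus lower split pools those lesions with every other surface of the same thirds.

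Size raises a smaller point. Section 2.4 admits differentiated tumors without ulceration at any size, so under a 20 mm split a lesion just above the cut and a very large one carry the same code.

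In a linear model, a prognostic baseline covariate removes residual variance and narrows the confidence interval for the treatment effect. A covariate that is already collected and is left out is precision forgone.

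**Working it through.** **Step 1. Reproduce the planned sample size.** Inputs from section 3.1: "82.2 ± 79.5 minutes vs 118.2 ± 71.6 minutes" for traction versus conventional ESD; the stated requirement, "142 patients were needed to ensure 80% power for a 2-sided significance level of 0.05"; and a planned total of 150 after a 5% allowance for dropout. Section 2.6 gives 1:1 allocation.

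- Difference: 118.2 − 82.2 = 36.0 min.
- Common SD: √[(79.5² + 71.6²)/2] = √5723.4 = 75.65 min.
- Standardized effect: 36.0/75.65 = 0.476.
- Normal approximation: n per arm = 2(1.960 + 0.842)²/0.476², which rounds up to 70, or 140 in total.
- Noncentral t: 71 per arm, or 142 in total, with power 80.4%. This matches the plan.
- Dropout: 142/0.95 = 149.5, rounded up to 150. This matches the plan.

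The SDs are raw, so 142 takes no credit for any covariate.

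**Step 2. Effect of extra covariates.** Let R₀ be the share of variance explained by the four planned factors and E the further share explained by the added terms. The document gives neither, so both are assumed: R₀ from 0% to 30% and E from 2% to 20%. At 71 per arm, by the normal approximation:

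- Power = Φ(0.476 × √(71/2)/√(1 − R₀ − E) − 1.960).
- Ratio of standard errors, new to planned = √[(1 − R₀ − E)/(1 − R₀)].

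| R₀ | Planned model | E = 2% | E = 5% | E = 10% | E = 20% |
|---|---|---|---|---|---|
| 0% | 80.9% | 81.7% | 82.9% | 84.8% | 88.7% |
| 10% | 84.8% | 85.6% | 86.8% | 88.7% | 92.3% |
| 20% | 88.7% | 89.4% | 90.6% | 92.3% | 95.5% |
| 30% | 92.3% | 93.0% | 94.0% | 95.5% | 98.0% |

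The gain runs from 0.7 points (92.3% to 93.0%) to 7.8 points (80.9% to 88.7%). The standard error falls by 1.0% (√0.98 = 0.990) to 15.5% (√(0.50/0.70) = 0.845).

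**Step 3. Greater curvature alone, as an illustration.** A yes/no factor with prevalence p and effect Δ, unrelated to the other covariates, explains p(1 − p)Δ²/SD². With an assumed p = 20% and Δ = 40 min this is 0.16 × 1600/5723.4 = 4.5%. That is near the E = 5% column, a gain of about 2 points.

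**Step 4. The 20 mm split.** If size acts linearly and is roughly normal, a split with share q below the cut c keeps φ(c)²/[q(1 − q)] of the variance that size explains. This is 64% for q = 50%, 58% for q = 70% and 49% for q = 80%. The document gives no size distribution, so these values of q are assumptions. They describe what one covariate retains, not a loss of power in this trial.

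**The case against.** The strongest reply is that nothing here is an error. Adjusting for all minimization factors is standard and valid, three of the five named drivers are already in the model, and nowhere does the article promise to adjust for every predictor. Surface and ulcer status are also examined in secondary analyses of procedure time. All of this stands, and it makes the point an improvement and not a correction. The secondary analyses do not sharpen the primary estimate, however.

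The coding is also inferred. Section 3.2 says only lesion location, and section 2.9 uses location for both third and surface. The reading as upper/middle versus lower rests on the model being tied to the stratification factors. The analysis plan, which is not shown, may settle this.

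A reader might infer more than the document supports:

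- **That the trial is underpowered.** It is not, on its own inputs. The large SD is already built into the 142. Showing gains only from an 80% start would also credit the four planned factors with no explained variance, against the Discussion's own list.
- **That the omission confounds the comparison.** In a randomized linear model, leaving out a baseline predictor does not bias the treatment effect, and chance imbalance is reflected in the standard error.
- **That all the extra variables are in hand.** Surface is. The trial's ulcer variable is read after resection, and section 2.4 implies a clinical ulcer judgement without defining an analysis variable. A pre-procedure size in millimetres is plausible but not stated: minimization needs only the side of 20 mm, and the tumor sizes listed as outcomes are histologic.
- **That operator skill needs finer modelling, such as a random intercept per operator.** Sections 2.7 and 2.8 let an expert take over from a trainee and count the time in the trainee's procedure, so one operator per case is not well defined. Section 2.7.1 admits any operator "who has performed more than 5 ESD procedures for gastric lesions", so the trainee group is broad, but the driver named in the Discussion is itself a threshold at 40 cases, almost exactly the split used.

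**Conclusion.** The point holds as a free improvement. The primary model omits a baseline predictor that the protocol names in its Introduction and Discussion and already records. The planned analysis remains valid and keeps its stated power.

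The precision forgone is real in direction but unquantified in the document. It is about 1 to 8 power points, or a standard error 1% to 15.5% smaller, if all added terms together explain a further 2% to 20% of variance beyond planned factors that explain 0% to 30%. Greater curvature alone would probably sit towards the lower end, as Step 3 illustrates. These figures assume a linear model with a common SD of 75.65 min and 71 evaluable patients per arm. The case for greater curvature is firm. The cases for ulcer finding and continuous size depend on what was recorded before the procedure.

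**What to change.** Keep the four minimization factors in the primary regression and state how each is coded. Add greater curvature (yes/no) as a prespecified covariate.

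Where the data were recorded before the procedure, also add the endoscopic ulcer finding, not post-resection pathology, and enter tumor size as a continuous measure in place of the 20 mm split.

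The statistical cost is small. With two institutions, the planned model has six coefficients (intercept, treatment and four two-level factors), leaving 142 − 6 = 136 residual degrees of freedom. Greater curvature takes one and ulcer finding another; recoding size as one linear term takes none. No new data collection is needed for greater curvature.

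The procedural cost is a documented amendment. Enrolment began in June 2021 and neither patients nor physicians are blinded, so the change should be dated and made before outcome data are examined.

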## AE reporting

4

### Definition of AE

4.1

An AE will be defined as any unfavorable or unintended illness or disability and its manifestations in a subject, regardless of whether it is casually related to the protocol treatment. If an AE is observed in a subject, then the principal investigator (or sub-investigator) will immediately ensure the safety of the subject, take appropriate measures, and describe the event in the case report. In this study, AEs will be reported from the date of obtaining informed consent to the end of the protocol 15 ± 7 days after ESD.

Post-ESD bleeding, perforation, and pneumonia after ESD will be assessed as defined above. AEs and reactions will be evaluated using American Society of Anesthesiologists guidelines^[26]^ and Common Terminology Criteria for Adverse Events v5.0 criteria.

### Serious AEs

4.2

Serious AEs will be defined as AEs occurring during or at any time after the procedure that results in death; is immediately life-threatening; requires in-patient hospitalization or prolongation of current hospitalization; results in persistent or significant disability or incapacity; or results in a congenital abnormality or birth defect.

The principal investigator at the institution where the serious AE occurs will take appropriate measures, regardless of whether or not there is a causal relationship between the AE and the treatment protocol. The investigator will immediately report the details of the event to the head of the research institution and the principal investigator of the study, in accordance with the regulations of the respective medical institution.

### Monitoring

4.3

Central monitoring will be performed once per year by an independent data monitoring committee. The monitoring committee will collect information on the status of accumulation, inclusion/exclusion criteria, serious AEs, and any other relevant information, and strive to provide feedback to participating institutions for early resolution if there are any problems.

## Discussion

5

Generally, ESD requires a professional endoscopist because of the need to maintain an appropriate view to dissect the submucosal layer, pre-coagulate thick blood vessels, and stop intra-operative bleeding rapidly. Because maintaining an appropriate submucosal view is the key to safe and rapid ESD, maintaining the appropriate tension on the submucosa for dissection using an endoscope hood or gravity is needed. Various traction devices have been developed to visualize the submucosal layer during ESD, thereby overcoming these technical difficulties.^[9–16]^

Ensuring the appropriate direction of traction, however, is important. For example, a recent multicenter RCT found that although procedure times did not differ significantly between patients who underwent the clip-with-line method and those who underwent conventional gastric ESD, the procedure times were shorter using the clip-with-line method for lesions located at the greater curvature of the upper and middle thirds of the stomach.^[17]^ These findings suggest that the traction direction may be limited. The clip-with-line method provides 1-way traction for the oral side through the cardia, enabling vertical traction for lesions located at the greater curvature. For other lesions, however, this method provides distal or proximal side traction and cannot view the appropriate submucosal layer for dissection in some patients.

The EndoTrac consists of a line with a clinch-knotted loop, a plastic sheath, and a T-shaped handle. After the line is tied to an endoclip, the distance between the endoclip and the tip of the plastic sheath can be adjusted by pulling or pushing the handle. Attachment of only the endoclip and the tip of the sheath to the lesion without a line would make it difficult to access the submucosal layer because of interference by the sheath. In the EndoTrac, however, the endoclip is tied to a line, providing greater access to the submucosal layer by pushing the sheath and extending the line.^[27]^

EndoTrac has advantages over clip-with-line traction methods. The EndoTrac can not only control the degree of strength but the direction of traction. Use of the EndoTrac enables coordination of an appropriate direction by pulling or pushing the sheath to achieve the desired traction. The clip-with-line method can pull but not push the lesion, with this 1-way traction resulting in inappropriate or excessive traction, preventing the operator from recognizing the appropriate submucosal layer for dissection.

To the best of our knowledge, the study described herein will be the first prospective randomized control study to compare the efficacy and safety of EndoTrac ESD with that of conventional ESD for gastric tumors. Use of a randomized controlled design can reduce biases associated with retrospective studies, such as patient selection, operator selection, small sample size, and the unconscious choice to use EndoTrac.

Factors associated with technical difficulties and long procedure times for gastric ESD include larger lesion sizes, lesions located in the middle and upper two-thirds of the stomach, lesions located in the greater curvature, presence of ulceration, and an operating physician who has performed <40 of these procedures.^[2,7,8,20–22]^ To determine whether these factors are also associated with greater difficulties in patients undergoing EndoTrac ESD, we plan to randomize patients to undergo EndoTrac or conventional ESD by dynamic balancing using the minimization method, and with stratification by operator experience (trainee vs expert), tumor size (≤20 mm vs >20 mm), tumor location (upper/middle thirds vs lower third), and institution (high vs low volume center). The major limitation of this study is that the operator is not blinded to treatment group allocation.

## Conclusions

6

This study is designed to assess whether EndoTrac ESD is superior to conventional ESD, thereby overcoming the technical difficulties of the latter. This study should resolve clinical questions of whether EndoTrac ESD is more effective and safer than conventional ESD.
